## Abstract

**Background:**

Major depressive disorder is the second leading cause of years lost to disability worldwide. Anyu Peibo Capsule has been shown to be effective and safe in phase II trials.

**Methods:**

This clinical study is a multi-center, randomized, double-blinded, placebo-controlled, parallel-group, phase III trial of Anyu Peibo Capsule in China. The aim is to test whether the administration of Anyu Peibo Capsule compared to placebo improves clinical outcomes in adults (aged 18 to 65 years) with MDD. Patients will receive an 8-week treatment of Anyu Peibo Capsule 1.6 g per day or placebo. The primary outcome will be the change from baseline in the total score for the Montgomery-Asberg Depression Rating Scale at the end of the 8-week treatment.

**Discussion:**

The trial aims to provide pivotal evidence for the efficacy and safety of Anyu Peibo Capsule in patients with major depressive disorder.

**Trial registration:**

ClinicalTrials.govNCT04210973. Registered on December 26, 2019

## Background

Major depressive disorder (MDD) is a recurrent, disabling, and serious psychological disorder and the second leading cause of years lost to disability worldwide (World Health Organization [1]). Over the past two decades, China has experienced rapid changes which have had a huge impact on the lifestyles and mental health of individuals. Current epidemiological investigations have shown that the lifetime prevalence of MDD in China has reached 3.4% [2], meaning that there are about 50 million people with MDD requiring appropriate treatment.

Antidepressants play a prominent role in the treatment of MDD [3]. The Chinese guidelines for depressive disorders recommend antidepressants as a first-line treatment for MDD [4]. However, about 30% of patients fail to achieve remission despite treatment with multiple antidepressants [5]. Treatment continuity is one of the main challenges in treating patients with MDD [6]. A national survey in China has shown that the top reason (36.1%) for why patients with MDD discontinue their medication is *concern about long-term side effects* [7]. There is a need to develop novel treatments for the relief of the symptoms of depression and to increase patients’ tolerance for long-term treatment.

Anyu Peibo Capsule is a new antidepressant, extracted from *Piper laetispicum* C. DC. (Piperaceae), a climbing glabrous plant growing in the south of China which has been used for invigorating the circulation and reducing detumescence and stasis, as well as having analgesic properties [8–11]. The pharmacodynamics of Anyu Peibo Capsule have been assessed in healthy volunteers. A favorable safety profile, a trend that the curative effect was higher than that of placebo, and remission rate in MDD have been demonstrated for Anyu Peibo Capsule in randomized, blinded, and placebo-controlled phase IIa and IIb trials.

The ongoing clinical study is a Chinese multi-center, randomized, double-blinded, placebo-controlled, parallel-group, phase III trial of Anyu Peibo Capsule administration in adults (aged 18 to 65 years) with MDD (AYPB-MDD-III). Based on the results of a phase II study, this trial is designed to detect clinically relevant differences in clinical outcomes at the end of the 8-week treatment as the primary endpoint.

## Methods

### Trial design

AYPB-MDD-III is a multi-center, randomized, double-blinded, placebo-controlled, parallel-group phase III clinical trial of Auyu Peibo Capsule to treat adults with MDD. This clinical trial is sponsored by Su Zhou YiHua Biotechnology Co. Ltd. and conducted at Shanghai Mental Health Center and 13 other sites in China (Appendix 1).

### Study objectives

The primary objective is to investigate the efficacy and safety of Anyu Peibo Capsule in comparison with placebo in adults with MDD. An exploratory objective is to explore potential predictive biomarkers for efficacy.

### Participants and eligibility

Patients diagnosed with MDD at the time of screening will be enrolled across 14 sites in China. The trial period will be from July 2019 to December 2020. The inclusion, exclusion, and withdrawal criteria in AYPB-MDD-III (Table 1) have been chosen to exclude patients at risk of suicide.

**Table 1 Tab1:** Inclusion criteria, exclusion criteria, and withdrawal criteria

Inclusion criteria	Exclusion criteria	Withdraw criteria
1. Adult (18~65 years old), outpatients or inpatients, male or female. 2. Patients with a primary diagnosis of major depressive disorder (MDD) based on the criteria of DSM-5, single episode or recurrent episode. 3. The total score of MADRS is ≥ 26 in both screening visit and baseline visit. 4. The first item of MADRS is ≥ 3 in both screening visit and baseline visit. 5. CGI-S is ≥ 4 in both screening visit and baseline visit. 6. The subject understands and consents to takes part in this clinical trial. The subjects should sign an informed consent form.	1. The subject has a current psychiatric diagnosis other than depression according to DSM-5, including schizophrenia spectrum disorders, bipolar and related disorders, anxiety disorders, obsessive-compulsive and related disorders, physical symptoms and related disorders, and other mental disorders. 2. The subject has a suicide attempt within the recent 1 year, has a currently significant risk of suicide, or has a score > 3 on item 10 (suicidal ideation) of MADRS. 3. The subject has a current depressive episode due to somatic general disease or a neurological disease, such as hypothyroidism. 4. When the MADRS total score of baseline visit compares with the screening visit, the decreasing rate is ≥ 25%. 5. Any unstable cardiovascular, hepatic, renal, blood, endocrine, or other medical diseases. 6. Any neurological disease (such as Parkinson’s disease, cerebrovascular accident, and epilepsy) or cerebral injury (traumatic or disease-related). Had a history or a high-risk related disease or medication of seizure disorder, except infantile febrile convulsion. 7. Known hypersensitivity to *Piper laetispicum* C. DC. or at least to two kinds of drugs. 8. Within 6 months before screening, there were addictions of alcohol and other substances (except nicotine). 9. The subject could not take medication or has a disease affecting drug absorption, distribution, metabolism, and excretion. 10. Clinically significant abnormal laboratory values (e.g., ALT or AST value above 2 times of clinical top limit; Cr value above normal top limit; thyroid gland function index (≥ 2 items in 5 items) above 1.2 times or below 0.8 times of the normal range, or investigator diagnosed with hypothyroidism or hyperthyroidism). 11. Clinically significant electrocardiographic (ECG) abnormalities in screening visit, such as QTc ≥ 450 ms in males or ≥ 470 ms in females. 12. The subject who used at least two different antidepressants with the recommended dose and adequate duration (maximum dosage by at least 4 weeks according to label) treatment still had no response. 13. The subject uses antidepressant drugs normally before 2 weeks of screening and stops using psychotropic drugs before randomization less than 5 half-life period (monoamine oxidase inhibitor: at least 2 weeks; fluoxetine: at least 1 month). 14. The subject received modified ECT, trans-cranial magnetic stimulation (TMS), vagus nerve stimulation (VNS), or systematic psychotherapy within 3 months. The subject received systematic light therapy, laser therapy and acupuncture, other traditional Chinese medicine, or systemic biofeedback therapy within 2 weeks. 15. Women who were pregnant, breastfeeding, or serum-HCG (+) on screening, or planning to become pregnant within 3 months after kick-off of the clinical trial. 16. Education level is below junior high school. 17. The subject has participated in a drug clinical trial within 1 month before screening. 18. The investigator thinks the subject is unsuitable to enroll in this clinical trial.	1. Occurrence of intolerable adverse events or serious adverse events. 2. Obvious protocol violation will impact the efficacy and safety assessment. 3. The subjects had symptoms of self-injury, suicide, manic episode, and with psychopathical feature. 4. The efficacy is not good. 5. The investigator determines to withdraw. 6. The subject will not continue the clinical trial or withdraw his/her informed consent. 7. Loss of follow-up. 8. Other circumstances in which the subject withdraw from the trial (such as changes in residence, which made it impossible to continue medication and follow-up).

Any of the following medications and treatments will be prohibited:
Other psychoactive drugs (except drugs permitted in the protocol), including antipsychotics, antidepressants, mood stabilizers, anti-anxiety drugs, and nootropicsTraditional Chinese medicines (including Chinese patent medicines and traditional Chinese medicine decoctions) which may have the effect of relieving depressionModified electroconvulsive therapy, transcranial magnetic stimulation, vagus nerve stimulation, light therapy, laser therapy, acupuncture, other traditional Chinese medicine treatments, biofeedback therapy, and other treatment methodsSystematic psychotherapy, such as psychoanalysis and cognitive behavior therapyOther medications and treatments that may significantly affect the efficacy and safety of antidepressants

Some combination therapies will be permitted:
For serious insomnia, zolpidem, zopiclone, S-Zopiclone, and zaleplon can be taken before sleep, as long as the dose does not exceed the upper limit specified in drug labels, and the cumulative dosing during the trial duration does not exceed 2 weeks.Medications used to treat physical diseases with efforts made to ensure the type and dosage do not change during the trial.

The following are the termination criteria of the trial:
There is a major design error in the protocol which makes it difficult to evaluate the drug effect.During the implementation of the trial, a major deviation occurs or an unexpected, serious risk to the patients is found.The ethics committee or sponsor decides to terminate the clinical trial.

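### No entry criterion requires exclusion of a current depressive episode with psychotic features, so such a patient can be randomized to placebo while antipsychotics and modified ECT are prohibited

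*Protocol article*

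**What the plan says.** All references are to the protocol article.

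**Entry (Table 1, Participants and eligibility).** Inclusion 2 asks for a "primary diagnosis of major depressive disorder (MDD) based on the criteria of DSM-5, single episode or recurrent episode". Inclusion 1 takes outpatients and inpatients. Inclusions 3 to 5 set minimum scores only: MADRS total at least 26, MADRS item 1 at least 3, CGI-S at least 4. Exclusion 1 begins "The subject has a current psychiatric diagnosis other than depression according to DSM-5, including schizophrenia spectrum disorders, bipolar and related disorders" and continues with further diagnostic groups.

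**Withdrawal (Table 1).** Criterion 3 reads "The subjects had symptoms of self-injury, suicide, manic episode, and with psychopathical feature". Criteria 4 and 5 read "The efficacy is not good. 5. The investigator determines to withdraw".

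**Treatment while in the trial.** The list of prohibited medications and treatments includes antipsychotics, other antidepressants and modified ECT. Randomization is 1:1 to study drug or placebo, and treatment lasts 8 weeks (Randomization; Trial interventions).

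**Risk control.** Participants and eligibility says that the criteria were chosen to keep out patients at risk of suicide. Justification for no concomitant therapy names suicide risk as its only entry exclusion. It adds that a patient whose condition worsens will be assessed, may leave at any time and will then receive standard treatment.

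**The concern.** A placebo-controlled trial that bars other active treatment depends on its entry criteria to keep out patients for whom that bar is unsafe. The article does this explicitly for suicide risk. It does not do so for a depressive episode with psychotic features, although antipsychotics and ECT are among the treatments it prohibits.

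Two things are at stake. The first is patient safety: someone already psychotic at baseline could be allocated to placebo, and the remedies would start only after randomization. The second is consistency: with no stated rule, 14 sites would rely on indirect filters and individual judgment, and could decide differently about similar patients.

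**Working it through.** The point involves no arithmetic. The check is a reading of every numbered criterion in Table 1 against one case: a patient with primary DSM-5 MDD whose current episode has psychotic features, and who meets the severity floors.

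**Premise.** An episode of this kind is still classified as major depressive disorder, not as a separate diagnosis. The article does not say this; it is a clinical assumption.

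**Criteria that bear on this patient**

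| Criterion | What it tests | Does it require exclusion? |
|---|---|---|
| Inclusion 2 | Primary DSM-5 MDD, single or recurrent | No; the patient qualifies |
| Inclusions 3 to 5 | Severity floors, no ceiling | No |
| Inclusion 6 | "The subject understands and consents to takes part in this clinical trial" | Only if understanding or consent is impaired |
| Exclusion 1 | Current diagnoses other than depression | No, under the premise |
| Exclusion 2 | Attempt within 1 year, or "has a currently significant risk of suicide, or has a score > 3 on item 10 (suicidal ideation) of MADRS" | Only if suicide risk is also present |
| Exclusion 12 | No response to at least two adequate antidepressant courses | Only with that treatment history |
| Exclusion 13 | Recent antidepressant use and washout: "stops using psychotropic drugs before randomization less than 5 half-life period" | Only through drug history, not symptoms |
| Exclusion 14 | Modified ECT and other listed treatments within set periods | Only with that treatment history |
| Exclusion 18 | "The investigator thinks the subject is unsuitable to enroll in this clinical trial" | Only if the investigator judges so; no condition is named |

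**Count.** Entry criteria that name psychotic features of the depressive episode: 0 of 6 inclusion and 0 of 18 exclusion criteria. Withdrawal criteria that plausibly do: 1 of 8 (criterion 3).

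**Withdrawal criterion 3 under each reading of its last term**

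- *Psychotic features.* This fits best beside self-injury, suicide and mania. The criterion is not limited to new onset, so a patient psychotic at baseline could be randomized and at once meet a reason to leave.
- *Personality pathology, or mania with such features.* Exclusion 1 then deals with entry, and criterion 3 says nothing about psychotic depression. The entry list still does not address it.

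The entry gap is therefore the same under every reading.

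**Timing of the other safeguards.** Withdrawal criteria 3 to 5, the patient's own right to leave, and DSMB safety review (Trial management, monitoring, and auditing) all act after randomization. The reassessment described in Justification for no concomitant therapy is tied to a decline in condition. A patient who is psychotic at entry and stays the same need not trigger it.

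**Sample size.** The stated 133 per group has no bearing on this point, and an added exclusion would not change it.

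**The case against.** The strongest case against is that this is an omission and that discretion already covers it.

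- **The source is a journal article.** It reports protocol version 1.2, which is not shown and may say more. This remains a caveat. But Table 1 prints full numbered lists with detail down to QTc limits and education level, so a dropped exclusion is possible but not the natural reading.
- **Psychiatrists would refuse such patients.** Research psychiatrists at psychiatric hospitals recruit, and exclusion 18 gives them a basis to refuse. Exclusions 12, 13 and 14 filter further. This limits the likely number. It does not close the gap, because exclusion 18 permits refusal without requiring it, and the sponsor did not leave suicide risk or bipolar disorder to that clause.
- **Withdrawal would follow quickly.** If criterion 3 does mean psychotic features, it applies at once and the treatment bar then ends. That stands. A reader might infer eight weeks of untreated psychosis. The article does not support that, since several exit routes would have to fail first.
- **The withdrawal list need not mirror the entry list.** Correct. A reader might infer a contradiction, because suicide and mania seem to have entry counterparts and the last term has none. The pattern is too weak for that. Withdrawal lists describe events on study, other withdrawal criteria have no counterpart at entry, and the counterpart for mania is indirect (bipolar disorders in exclusion 1). The term itself is an ambiguous translation.
- **The harm is not quantified.** Also correct. The article gives no share of candidates with psychotic features and does not say what treatment they need. That sites would actually differ is a possibility, not something shown.

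**Conclusion.** The point holds as a safety and eligibility gap. As listed, the criteria admit any primary DSM-5 MDD without an upper severity limit, and none requires exclusion of a current depressive episode with psychotic features. Such a patient could be randomized to placebo and barred from antipsychotics and modified ECT until withdrawn. Withdrawal criterion 3 lends support under its most plausible reading, but the conclusion does not need it.

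Severity is minor to moderate. The number of patients affected cannot be derived from the document. The 1:1 ratio gives each randomized patient a 50% chance of placebo, but that holds for every participant and does not measure this problem. A reader might also infer a loss of power or a biased treatment estimate; nothing in the article allows either to be sized, and neither is claimed.

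The conclusion rests on two assumptions: that a depressive episode with psychotic features counts as MDD under inclusion 2, and that Table 1 reproduces the full protocol's criteria. Confidence is medium.

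**What to change.** 1. Add one exclusion to Table 1: *current depressive episode with psychotic features*.
2. Reword withdrawal criterion 3: *emergence of self-injury, suicidal behaviour, a manic episode or psychotic features during treatment*. This replaces the ambiguous term and makes clear that the criterion covers events on study.

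The cost is low: one added line, one wording correction and a few more screen failures. The DSM-5 diagnosis is already made at screening, so no new procedure is needed. Trial status describes recruitment as still under way, so an amendment at that stage could still protect patients not yet enrolled. If the full protocol already contains such an exclusion, only the wording of criterion 3 needs to change.

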### Justification for no concomitant therapy

This trial is designed according to *Major Depressive Disorder: Developing Drugs for Treatment Guidance for Industry (FDA 2018)* [12] to develop a new drug. Following this guidance, randomized, double-blind, placebo-controlled, parallel designs are recommended as the current standard for short-term efficacy trials in MDD. When this trial was to be designed as no concomitant therapy, actions for risk control and management were included in the first consideration. Therefore, we will exclude those who are at risk of suicide and ensure appropriate and sufficient informed consent process. What is more, when the patients’ condition declines due to no treatment, the condition will be assessed to decide whether to unblind or not, the patient could withdraw at any moment, and then standard treatment will be provided.

### Randomization

Patients enrolled in the AYPB-MDD-III trial are allocated to treatment with Auyu Peibo Capsule or placebo in a 1:1 ratio via the clinical trial electronic central stochastic system (DAS) for interactive web response system (IWRS).

### Trial interventions

Auyu Peibo is a capsule containing 20 mg of extracts (main ingredient: amide alkaloids); the taste- and visual-masked placebo is an identically shaped capsule containing no effective materials. Four tablets of the study drug or placebo will be administered orally, with water, 30 min after breakfast and supper, twice per day for 8 weeks. The patient’s adherence is monitored and assessed by the percentage of the number of practical drugs to the number of prescribed drugs.

The patient flow is displayed in Fig. 1 according to the Consolidated Standards of Reporting Trials (CONSORT) [13] diagram, and the SPRIT [14] scheme of study procedures is shown in Fig. 2.

**Fig. 1 Fig1:**
[figure not shown]
Participant flow through the AYPB-MDD-III

**Fig. 2 Fig2:**
[figure not shown]
SPRIT scheme of study procedures

### Blinding

AYPB-MDD-III is double-blinded. Patients, care providers, investigators, and outcome assessors will not know the treatment allocation. The investigated drug is prepared by the central pharmacy and will be provided as a ready-to-use drug or placebo, labeled with a random number and patient number. The placebo is taste- and visual-masked. Emergency unblinding can be conducted via DAS for IWRS. Unblinding under emergency will be permissible due to a serious adverse event, or for the purpose of notification to the Data and Safety Monitoring Board (DSMB).

### Recruitment

Patients will be recruited from 14 sites (psychiatric hospitals) in China, where research psychiatrists and clinical staff from each site will invite potential patients to participate in the study.

### Data management and quality assurance

Trained research psychiatrists from each site will record the collected data on a source document and a web-based eCRF (DAS for EDC V6.0, in Chinese). Verification and cross-checking of the eCRF will be conducted by the study monitor, who will be provided by the site clinical research organization as well as the sponsor. Omissions, errors, and values requiring further clarification will be reviewed. Corrections should be made only by authorized personnel and be documented in an audit trail.

### Strategies to improve adherence to interventions

Reminder texts will be sent to patients before each study visit, and fees for public transportation will be reimbursed for attendance.

### Provisions for post-trial care

There will be no special post-trial care, and patients will continue their usual health care when the trial has been finished.

### Data collection methods

#### Study instruments

##### Chinese version of the Montgomery-Asberg Depression Rating Scale (MADRS)

The Chinese version of the MADRS [15, 16] has been translated from the original English version. It consists of 10 items rated on a 0–6 continuum (0 = no abnormality, 6 = severe) to assess the core symptoms of depression. Inter-rater reliability on the Chinese MADRS with different pairs of raters has been reported to be 0.954; reliability, validity, and sensitivity have been demonstrated to be good [17].

##### 17-item Hamilton Depression Scale (HAMD-17) Chinese version

The Chinese version of the HAMD-17 has been translated from the original English version. It consists of 17 items that are rated to assess the symptoms of depression. The Chinese HAMD-17 Cronbach’s alpha coefficients are calculated to be over 0.70, and internal consistency and validity have been demonstrated to be good [18].

##### Chinese version of the Sheehan Disability Scale (SDS)

The Chinese SDS measures impairment in work/school, social life, and family life responsibilities. The Chinese version of the SDS has been reported to have good validity and reliability [19].

### Primary outcome

The primary outcome is the change from baseline in the MADRS score following the 8-week treatment period.

